## Abstract

**Introduction:**

Postoperative recurrence and metastasis of gastric cancer (GC) are primary factors that contribute to poor prognosis. GC recurs at a rate of approximately 70%–80% within 2 years after local treatment and approximately 90% within 5 years. “*Yang-deficient toxic node*” is the core pathogenesis of GC recurrence and metastasis. The *Yiqi Wenyang Jiedu* prescription (YWJP), a form of complementary and alternative medicine in China, is an empirical remedy to prevent postoperative recurrence and metastasis of GC. Taking the main therapeutic principles of “nourishing *Qi* and warming *Yang*, strengthening *Zhengqi*, and detoxifying” can aid in preventing the recurrence and metastasis of GC in patients during the watchful waiting period after surgery and adjuvant chemotherapy. This approach aims to enhance the quality of life of patients. However, high-quality evidence to support this hypothesis is lacking. This study will aim to investigate the efficacy and safety of YWJP to prevent and treat postoperative metastasis and GC recurrence.

**Methods:**

The study will be a multicenter, randomized, double-blind, placebo-parallel-controlled clinical trial. A total of 212 patients who completed adjuvant chemotherapy within 8 months of radical gastrectomy will be enrolled. Patients in the intervention group will receive the YWJP, whereas those in the control group will receive a placebo. The main outcome was the disease-free survival (DFS) rate 2 years after surgery. The secondary outcomes included DFS time, overall survival, annual cumulative recurrence and rate of metastasis after 1–3 years, cumulative annual survival after 1–3 years, fat distribution-related indicators, tumor markers, peripheral blood inflammatory indicators, prognostic nutritional index, symptoms and quality of life evaluation, medication compliance, and adverse reaction rate.

**Discussion:**

There is a lack of effective therapy after the completion of adjuvant therapy during the postoperative period of watchful waiting. This study will be the first randomized clinical trial to evaluate whether complementary and alternative medical interventions can effectively prevent recurrence and metastasis during the watchful waiting period after GC surgery and to provide evidence for surveillance treatment management after GC surgery.

**Clinical trial registration:**

ClinicalTrials.gov, identifier NCT05229809.

## Highlights

QuestionCan *Yiqi Wenyang Jiedu* prescription reduce the rate of recurrence and metastasis in patients with gastric cancer during the watchful waiting period after surgery?FindingsThis randomized clinical trial will involve 212 patients with GC who completed adjuvant chemotherapy after surgery. The primary outcome was disease-free survival at a rate of 2 years after surgery.MeaningThis ongoing clinical trial will supply the treatment management during the watchful waiting period after GC surgery and provide evidence for the effectiveness of complementary and alternative medicine in reducing recurrence and metastasis rates after GC surgery.

## Introduction

1

Gastric cancer (GC) is a common malignant tumor of the digestive system, and according to the Global Cancer Statistics 2022, the number of new GC cases worldwide is 968,350, ranking fifth among all malignancies. The number of deaths was 659,853, ranking fifth among all cancer types (1, 2). China has the highest cancer burden worldwide, according to the National Cancer Center of China (3), and they projected that an estimated 4,824,700 new cancer cases and 2,574,200 new cancer deaths will occur in China in 2022. Among these, GC ranked fifth and third among new cases and deaths, respectively. Despite a decline in GC incidence observed in many countries, the total number of GC cases worldwide shows a slow upward trend, particularly in China (4, 5). Even more terrifying is that the global burden caused by the rising trend of GC cases is expected to increase by 62% to 1.77 million cases in 2040 (6). Studies have confirmed that various factors such as *Helicobacter pylori* infection (7), cigarette smoking (8, 9), heavy alcohol consumption (10–12), sex (13), obesity (14, 15), metabolic dysfunction (16, 17), and so on (18–26) are recognized as major risk factors for GC incidence.

Surgery is currently the preferred treatment for GC. The National Comprehensive Cancer Network guidelines (2023. V1) recommend that patients with stage pT3–4 cancer, any N, should undergo post-surgical chemoradiotherapy followed by a period of surveillance and management (27–39). Approximately 70%–80% of patients with GC relapsed within 2 years after local therapy. The median recurrence time for GC is approximately 16.8 months (40–42). Previous studies have shown that *Yang* deficiency is one of the main syndromes of GC (43), *Yang* deficiency and a low metabolic state can stimulate cancer cells to induce metabolic reprogramming and promote postoperative recurrence and metastasis of GC (44–48). Therefore, during the period between postoperative recovery and the onset of GC recurrence and metastasis, identifying effective treatment strategies is crucial and requires urgent attention.

Complementary and alternative medicine is a safe and effective potential choice that can improve the overall survival (OS) of patients with GC (49–51). Previous studies have indicated that patients with GC who experience *Qi* and *Yang* deficiencies after surgery are more susceptible to recurrence and metastasis than those with no *Qi* and *Yang* deficiencies (52, 53). The *Yiqi Wenyang Jiedu* prescription (YWJP) follows the treatment principles of nourishing *Qi* and warming *Yang*, strengthening *Zhengqi*, and detoxifying, and can improve the physical condition and alleviate clinical symptoms in patients with *Yang* deficiency (54, 55). YWJP may improve patients’ low metabolic state by regulating the tumor microenvironment and delaying or reversing recurrence and metastasis. Therefore, we plan to conduct a multicenter, randomized, double-blind, placebo-parallel-controlled clinical trial that will apply YWJP, an effective prescription for the prevention and treatment of recurrence and metastasis of postoperative GC at the Guang’anmen Hospital of China Academy of Chinese Medical Sciences, and explore its mechanisms.

## Materials and methods

2

### Design

2.1

The multicenter, randomized, double-blind, placebo-parallel-controlled clinical study will be conducted at seven hospitals, including Guang’anmen Hospital of the China Academy of Chinese Medical Sciences, Jiangsu Provincial Hospital of Traditional Chinese Medicine (TCM), the First Affiliated Hospital of Guangzhou University of Chinese Medicine, and Yueyang Hospital of Integrated Traditional Chinese and Western Medicine Affiliated to Shanghai University of Chinese Medicine. After signing the informed consent forms, 212 participants will be randomly assigned to the intervention group (YWJP) or the control group (YWJP placebo).

The key herbs of YWJP include *Astragalus membranaceus* (30 *g*)*, Codonopsis pilosula* (15 *g*)*, Angelica dahurica* (10 *g*)*, Curcuma zedoary* (9 *g*)*, Rhizoma nardostachyos* (10 *g*)*, Polygonum cuspidatum* (10 *g*)*, Radix Actinidiae chinensis* (15 *g*), and *Paris polyphylla* (9 *g*) (108 g in total). The control group will receive a YWJP placebo intervention comprising maltodextrin, lactose, bitters, citric acid, and other edible-grade raw materials (108 g in total). All experimental herbs and placebos used in this study will be provided by Jiangyin Tianjiang Pharmaceutical Co., Ltd. All raw materials have undergone safety assessments and quality inspection reports have been issued. YWJP and its placebo have been confirmed to be safe, reliable, controllable in quality, and similar in shape, color, smell, and taste.

The primary and secondary outcomes will be evaluated immediately at the end of the follow-up period. The study process is illustrated in **Figure 1**. The clinical trial protocol complied with the Clinical Trial Standard Protocol Items: Recommendations for Interventional Trials (56) and Consolidated Standards of Reporting Trials (CONSORT) (57).

**Figure 1 f1:**
[figure not shown]
CONSORT flow diagram.

### Recruitment

2.2

We plan to recruit patients from seven traditional Chinese oncology hospitals nationwide, led by Guang’anmen Hospital, and enroll patients by following up with expert clinics, playing recruitment advertisements on hospital LED screens, and posting recruitment posters. When we encounter potential patients, we will introduce our study protocol, including the objectives, intervention methods, processes, and potential adverse reactions. The research team will conduct repeated screenings of patients on a two-person basis. Patients who meet the inclusion criteria and wish to voluntarily participate in the study will sign an informed consent form.

### Study population

2.3

The diagnostic criteria for GC, according to the 2021 Chinese Society of Clinical Oncology (CSCO), will be followed. The diagnosis and treatment of GC follow the clinical guidelines outlined in the 8th edition of the International Union Against Cancer (UICC) classification system (58).

### Inclusion criteria

2.4

1. Research cases must be sourced from real-world registration platforms.2. Stage II–III non-esophageal gastric junction GC that meets the diagnostic criteria and does not indicate tumor recurrence or metastasis by imaging.3. Patients with GC who underwent radical gastrectomy (R0) within 8 months after surgery and completed at least six cycles of adjuvant chemotherapy with standard regimens (XELOX and SOX).4. Eastern Cooperative Oncology Group (ECOG) performance status score of 0–2.5. Patient ages ranging from 18 to 75 years, with no sex limitations.6. Expected survival time ≥3 months.7. Patients who voluntarily participated in the study, signed an informed consent form, and participated in the follow-up.

### Exclusion criteria

2.5

1. Patients with concomitant primary tumors in other areas.2. Patients with GC who were pathologically diagnosed with adenosquamous carcinoma, lymphoid interstitial carcinoma (medullary carcinoma), hepatoid adenocarcinoma, squamous cell carcinoma, signet ring cell carcinoma, undifferentiated carcinoma, and other gastric malignancies, such as gastric neuroendocrine tumors, gastric interlobular tumors, and gastric malignant lymphoma.3. Patients who received neoadjuvant chemotherapy before surgery.4. Patients who have been and are currently receiving targeted drug therapy.5. Patients who have undergone or are currently undergoing gastric radiation therapy.6. Patients who have undergone or are currently undergoing tumor immunotherapy.7. Patients with mental illness.8. Patients with severe and uncontrollable organic lesions or infections such as decompensated heart, lung, or kidney failure, who cannot tolerate chemotherapy.9. Patients who underwent clinical trials of small-molecule drugs within 28 days or large-molecule drugs within 3 months.10. Patients who are known to be allergic or intolerant to the study drug.

### Criteria for withdrawal and removal

2.6

1. Those who experienced unexpected events during the treatment process and were unable to adhere to the protocol.2. Patients who voluntarily requested withdrawal.3. The researchers judged patients who exhibited poor compliance and were unable to continue clinical research.4. Patients experiencing pregnancy, death, or loss of follow-up.

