### Criteria for discontinuation

2.10

If unexpected adverse events occur, participants should no longer follow the study guidelines for such events. The investigator should comprehensively analyze whether these events are related to the experimental and control drugs used, and should decide whether to discontinue the clinical trial based on the participant’s condition. Patients who discontinue trials owing to serious adverse events should be followed up, and their outcomes should be documented. In addition, participants who could not adhere to the treatment and those who requested active withdrawal, had poor compliance, were pregnant, dead, or lost to follow-up met the criteria for discontinuation.

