#### Primary outcome

2.12.1

The primary outcome of this study is the 2-year DFS rate after surgery, which refers to the proportion of patients who have not experienced recurrence, metastasis, or (for any reason) death within 2 years after surgery.

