### Statistical analysis and method

2.16

SAS 9.4 statistical software will be used, and full analysis set (FAS) and protocol compliance set (PPS) analyses will be performed on the efficacy indicators. A safety dataset analysis should be conducted for adverse reactions. All statistical tests will be conducted bilaterally, and statistical significance will be set at *p* ≤ 0.05. We will analyze whether there are outliers in the data and conduct a professional analysis of outliers to decide whether to accept or reject them. After this, we will analyze the data for missing values and conduct a professional analysis to determine whether the missing values are listed as missing or data transferred. The proportion of shedding cases should not exceed 10%; otherwise, analysis and explanation should be provided. The measurement data were described as mean, standard deviation, median, minimum, and maximum whereas counting data were described as frequency, percentage, etc. Quantitative data analysis will be performed using *t*-tests, rank-sum tests, etc. Counting data analysis will be performed using chi-square tests, ridit analyses, etc. Survival data analysis will be performed using the Kaplan–Meier method, Wilcoxon rank sum test, or log-rank test. A Cox-proportional risk regression model was used for multivariate survival analysis.

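### Death, poor compliance and voluntary withdrawal share one removal list, which conflicts with death as an endpoint and leaves patients removed early without clearly stated recurrence follow-up

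*Protocol article*

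**What the plan says.** Section 2.6 (Criteria for withdrawal and removal) has four items: unexpected events that prevent adherence; voluntary withdrawal; "The researchers judged patients who exhibited poor compliance and were unable to continue clinical research"; and "Patients experiencing pregnancy, death, or loss of follow-up". Section 2.10 (Criteria for discontinuation) gives nearly the same list: besides patients who could not adhere or who asked to withdraw, those who "had poor compliance, were pregnant, dead, or lost to follow-up met the criteria for discontinuation".

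On what happens afterwards, Section 2.10 says only this: "Patients who discontinue trials owing to serious adverse events should be followed up, and their outcomes should be documented". Section 2.14 states that patients are observed for at least 3 years after surgery. Its imaging sentence (every 3 months to 2 years after surgery, then every 6 months) is written for participants without progression who have completed six courses.

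On the outcomes, Section 2.12.1 defines the primary 2-year DFS rate as "the proportion of patients who have not experienced recurrence, metastasis, or (for any reason) death within 2 years after surgery". Section 2.12.2 counts death from any cause as an event for DFS time and as the sole event for OS.

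**The concern.** Three different things sit in one category: stopping study drug, leaving follow-up, and reaching an endpoint. A site that works from Sections 2.6 and 2.10 could close a patient's record at removal. For a death, that conflicts with the outcome definitions. For a patient removed for poor compliance or inability to adhere, it may end recurrence imaging long before the 2-year assessment.

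The second case is the more practical risk. Removal happens after randomisation, rests partly on the investigator's judgement, and may depend on tolerability or on early symptoms of relapse. If either differs by arm, the patients whose 2-year status is known are no longer comparable groups, even with sound randomisation and blinding.

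**Working it through.** **1. The plan's own figure.** Inputs from Section 2.11: DFS 43.9% versus 63.9%, two-sided alpha 0.05, power 80%, 1:1 allocation. The pooled two-proportion formula, with mean proportion 0.539, is

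n = [1.96 × √(2 × 0.539 × 0.461) + 0.842 × √(0.639 × 0.361 + 0.439 × 0.561)]² / 0.20² ≈ 96.3 per arm.

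The plan states 96, which reproduces. Adding 10% gives 96 × 1.1 = 105.6, so 106 per arm. The point does not depend on this number, and the fix does not change it.

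**2. The passages side by side.**

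| Situation | Sections 2.6 and 2.10 | Other sections |
|---|---|---|
| Death | Removal / discontinuation | Primary DFS failure, DFS-time event, only OS event (2.12.1, 2.12.2) |
| Poor compliance, cannot adhere | Removal / discontinuation; no later follow-up stated | Observed at least 3 years (2.14); imaging sentence covers completers of six courses |
| Serious adverse event | Discontinuation, with follow-up stated | Consistent |
| Voluntary request | Removal / discontinuation | Drug withdrawal and follow-up withdrawal not distinguished |

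No section says which rule prevails in the first two rows.

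**3. How much observation is at risk.** Treatment is six courses of 4 weeks (Section 2.8), or 24 weeks: 24 × 7 / 30.4 ≈ 5.5 months. Entry is within 8 months of surgery (Section 2.4). For a patient randomised at 8 months:

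- Treatment ends at about 8 + 5.5 = 13.5 months after surgery, which leaves 24 − 13.5 = 10.5 months to the primary time point.
- If the patient is removed after one course (28 / 30.4 ≈ 0.9 months), 24 − 8 − 0.9 ≈ 15.1 months remain without a clearly stated imaging schedule.

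The Introduction gives a median recurrence time of about 16.8 months. If that is counted from surgery (an assumption), it falls after treatment ends, so much of the recurrence to be counted lies in the part that could be lost.

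**4. Conditional worst case for deaths.** Two assumptions that are not in the document: a share f of 2-year DFS failures are deaths, equal in both arms; and those patients' whole records are deleted. With planned DFS rate S, apparent DFS = S / [1 − f(1 − S)]. Planned failures are 56.1% (control) and 36.1% (intervention); 106 per arm.

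| f | Control | Intervention | Difference (points) | Patients deleted | Power |
|---|---|---|---|---|---|
| 0 | 43.9% | 63.9% | 20.0 | 0 | 83.7% |
| 20% | 0.439/0.8878 = 49.4% | 0.639/0.9278 = 68.9% | 19.4 | 19.5 | 78.7% |
| 30% | 0.439/0.8317 = 52.8% | 0.639/0.8917 = 71.7% | 18.9 | 29.3 | 75.3% |
| 50% | 0.439/0.7195 = 61.0% | 0.639/0.8195 = 78.0% | 17.0 | 48.9 | 65.6% |

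Under these assumptions both rates rise, more control than intervention patients disappear, and the difference shrinks. The loss from early removal for compliance cannot be sized in the same way, because neither its frequency nor its relation to recurrence is given.

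**The case against.** The strongest reply is that Sections 2.6 and 2.10 only list the ways in which participation can end, and death is naturally one of them. No section says that removal means deletion from the analysis. The outcome definitions count death explicitly. Table 1 marks survival status as required at every visit, and its follow-up column marks CT-type imaging as required without limiting it to completers. Section 2.12.2 tabulates patients with compliance below 80%, so low compliers are expected in the data. The poor-compliance item also requires inability to continue. Section 2.16 plans both a full analysis set (FAS) and a per-protocol analysis.

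Much of this stands, and it rules out several stronger readings that a reader might infer:

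- That deaths will be deleted and OS left without events. The text does not say so. A patient who relapsed before dying would already be a DFS failure, so step 4 is a worst case and not the plan.
- That removals, including deaths, use up the 10% allowance. The line "The proportion of shedding cases should not exceed 10" (per cent) neither defines shedding nor refers to Section 2.6, and it does not mention death.
- That the FAS breaks randomisation. The article does not define the FAS, and that definition may properly sit in a document not shown.

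The reply does not remove the conflict. The general 3-year statement and Table 1 do not say that they override removal, while the specific sentences name only serious adverse events and completers of six courses.

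**Conclusion.** The point holds as a conflict within the current text and a gap in ascertainment. Death cannot be both a reason for removal and a counted event unless the document says which governs. Patients removed early for compliance or inability to adhere have no clearly stated recurrence follow-up to 2 years. That loss would be informative and could differ by arm.

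The size of any bias cannot be computed from the document. The range of 49% to 61% versus 69% to 78% DFS depends on an assumed 20% to 50% death share and on deletion of whole records, neither of which the document states. The conclusion itself rests only on the wording of Sections 2.6, 2.10, 2.12 and 2.14.

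**What to change.** Reconcile the passages as follows:

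1. Take death out of the lists in Sections 2.6 and 2.10 and state that it is an endpoint event for DFS and OS.
2. Define two separate categories: stopped study drug, and withdrew consent for follow-up.
3. In Sections 2.10 and 2.14, apply the existing 3-monthly follow-up and the imaging schedule to every randomised patient, whatever the adherence or number of courses completed, unless consent for follow-up is withdrawn. Keep these patients in the FAS.

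True loss to follow-up cannot be removed by wording and remains a matter for the analysis. The cost is a wording amendment plus continued contact and already scheduled imaging for patients who stop drug. The sample size is unchanged.

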### Randomization and blinding

2.7

This study will apply an Interactive Web Response System for central randomization and implement hidden allocation schemes. Patients will be randomly divided into intervention and control groups in a 1:1 ratio based on central randomization. The R software (V3.3.3) will be used to generate random sequences with three rounds of cyclic random statements. The blinding level will be double-blind, in which neither the researcher nor the participant have any idea of the specific details of the study. Anonymizing will be performed by statisticians who did not participate in the clinical trials and divided into two levels. This trial will establish a dedicated “emergency letter” for clinical trials that can only be urgently unblinded when the patient experiences an emergency. Handling this situation requires a clear understanding of the patient’s medication information.

### Intervention

2.8

The intervention group will receive YWJP, whereas the control group will receive YWJP placebo. Patients will take one pack each time, dilute it with boiling water, and administer it twice daily (in the morning and evening). The course of treatment will be 4 weeks, and six courses are planned.

### Criteria for adherence

2.9

After enrollment, patients will take their medication according to the method described in the “intervention” section. During the intervention, symptoms such as nausea, vomiting, liver and kidney dysfunction, diarrhea, and infection will be treated with medication. However, specific symptoms and combined medications must be recorded. Receiving modern antitumor treatment (including chemotherapy, immunotherapy, molecular targeted therapy, and radiotherapy) or taking other Chinese herbal decoctions, Chinese herbal injections, and traditional Chinese patent medicines with antitumor effects during the intervention will be prohibited.

